## 4. MEASUREMENTS

### 4.1 Anthropometry

#### 4.1.1 Weight, height, and waist circumference

The child will be weighed on a digital scale with the child in underwear. Standing height will be measured three times to the nearest millimeter with a stadiometer. Waist circumference will be measured three times to the nearest millimeter by a non-elastic measuring tape at the level of the umbilicus. The mean of three measurements will be used for height and waist circumference.

#### **4.1.2 Body composition**

Fat mass and fat-free mass will be measured by bio impedance with the child lying down without moving after 10 minutes rest, if possibly with empty bladder. Four electrodes will be placed at the dorsal surface of the right hand and foot. The measurement takes about 2 minutes after electrodes have been placed. Fat mass will also be measured by three repeated skinfold measurements at triceps and subscapularis, respectively, while the child is standing.

### **4.2 Cardiovascular function**

#### **4.2.1 Blood pressure and heart rate**

Blood pressure and heart rate will be measured three times by an automated device with the child lying down after 10 minutes rest. The appropriate cuff size for the child's arm circumference will be used. This procedure will be repeated up to four times during the five hour baseline and endpoint visits to account for potential variation in blood pressure during the visits and thereby obtain the most accurate measure of the primary outcome.

#### **4.2.2 Continuously measured heart rate by electrocardiograms (ECG)**

Throughout the baseline and endpoint visits, electrocardiograms will be recorded continuously by a Holter monitoring recorder device. When the child has arrived at the department four electrodes will be placed on the chest of the child. Electrodes will be removed again by the end of that examination visit. The recordings will be analyzed at Department of Clinical Medicine, Aalborg University Hospital, by [name] ([name]).

### **4.3 Cognitive function, behavior, and emotions**

We will use a number of computer (e.g. Flanker's and test from the CANTAB battery: <http://www.cambridgecognition.com/academic/cantabsuite/tests>) and paper based test (e.g. Stroop, and D2 (Appendix 12)) to assess specific areas of cognitive function focusing on memory, attention, and reaction time. The tests are internationally recognized, validated and standardized tests that will be adjusted to the children's age. Children's physiological stress response will be assessed using a cold pressor test, where the child submerges his/her dominant hand in a tub containing water (temperature  $5^{\circ}\text{C} \pm 2^{\circ}\text{C}$ ) for maximum 1 minute. Before and immediately after the test we measure the child's blood pressure and heart rate, and before and 20 min after the test we collect a salivary sample to be analyzed for cortisol concentration. Together with the heart rhythm recorded continuously during the test (see 4.2.2), these outcomes will be used to assess the child's overall physiological stress response. Children are instructed that they can remove their hand from the water if they find the test too uncomfortable and will be reminded about this during the test if they display discomfort. Cognitive, behavioral and emotional outcomes will also be measured by validated questionnaires to be filled in by the parents (Appendix 9-11). A pre-test prior to the baseline visit will be performed for some of the cognitive tests to avoid interference by learning effects. Prior to testing the project staff will instruct the children on how to do the tests.

Trained project personnel will conduct interviews with the children based on the Kid-KINDL questionnaire (Appendix 20) assessing children's quality of life. Parents might be asked to fill in some of the questionnaires at home prior to the baseline and endpoints visits to assure that the same

parent answer the questions at both visits (Appendix 9-11). Assessments of cognitive function, behavior, and emotions will be supervised by psychologist, PhD, [name].

#### **4.4 Pubertal stage**

At baseline pubertal stage will be evaluated by the parents, if necessary aided by the child, using a self-administered questionnaire on breast development and age at menarche for girls (Appendix 13) and pubic hair for boys (Appendix 14).

#### **4.5 Dietary intake**

The children's dietary intake will be recorded by the parents prior to the baseline and endpoint visits during four days of weighed dietary recording registered in a web based program ([www.madlog.dk](http://www.madlog.dk)). Parents will be instructed on how to weigh and record the children's dietary intake during the pre-visit at NEXS (Appendix 15). If weighing of the food is not possible, parents will be asked to indicate household measures. If the parents do not have a digital kitchen scale at home it will be possible to borrow one from the study site. Also, during the 12 week intervention period the parents will be asked to register the children's intake of study products weekly. The children's habitual intake of fish, poultry and meat will be examined by a food frequency questionnaire (Appendix 19) filled in by the parents before the baseline and endpoint visits.

#### **4.6 Physical activity and sleep**

The children's physical activity and sleep will be measured by accelerometers during 7 consecutive days and 8 nights prior to the baseline and endpoint visits. During the pre-visit parents and children will be instructed on how to use the accelerometers (Appendix 17).

#### **4.7 Fasting and standardized breakfast**

The children will be asked to meet for the baseline and endpoint visits fasting (Appendix 18). That is they are not supposed to consume foods or drinks with calories from midnight the night before the visits. After the cardiometabolic measurements breakfast will be provided to the child. The same type of breakfast will be provided at the baseline and endpoint visit to ensure minimum influence on the subsequent cognitive measurements. If a child does not like the breakfast served he or she is allowed to bring breakfast from home, but the family will be instructed to bring the same type of breakfast at both visits.

#### **4.8 Biological samples**

##### **4.8.1 Blood samples**

Before the baseline and endpoint visits parents will receive local anesthetic EMLA patches with instructions on how to apply them (Appendix 18). At each visit 40 ml venous blood will be drawn from the child's forearm after removal of the patches. Samples will be processed and stored at NEXS at  $-80^{\circ}\text{C}$  until analysis. Following analysis the remaining samples will be destroyed, unless separate consent for storage of remaining blood in the biobank has been given.

#### 4.8.2 Hair sample

A small tuft of hair (approximately 5-20 mg) will be cut with a pair of scissors from the posterior vertex of the child's head. The three centimeters of the hair strands located most closely to the scalp will be used for analysis of cortisol, reflecting cortisol levels over the last 3 months.

#### 4.8.3 Salivary sample

The salivary samples (2 x approximately 0.5-2 ml) will be collected before and after the cold pressor test using a small swab which the child will chew for about 60 seconds to stimulate salivation. Saliva samples will be centrifuged and stored at NEXS at maximum  $-20^{\circ}\text{C}$  until analysis of cortisol. The salivary cortisol level reflects the acute serum cortisol level.

#### 4.8.4 Analysis of biological samples

**Table 2** gives an overview of the planned analyses of the biological samples.

**Table 2. Biological sample analyses**

| Samples          | Field           | Analyses                                                                                                                                                                                                                                         |
|------------------|-----------------|--------------------------------------------------------------------------------------------------------------------------------------------------------------------------------------------------------------------------------------------------|
| Blood samples    | Cardiometabolic | 
 
• Triacylglycerol and cholesterol
 
• Glucose, insulin, and glycosylated haemoglobin (HbA1c)
 
• C-reactive protein, adipokines, and related markers
 
                             |
|                  | Compliance      | 
 
• Fatty acid composition and lipid species
 
                                                                                                                                                     |
|                  | Nutrient status | 
 
• Serum 25(OH) vitamin D, vitamin D metabolites and binding proteins
 
• Haemoglobin and ferritin
 
• Other nutrient biomarkers
 
                                                  |
|                  | Immune          | 
 
• Immune cells, cytokines and other immune markers
 
                                                                                                                                             |
|                  | Hormones        | 
 
• Sex hormones, appetite hormones
 
                                                                                                                                                              |
|                  | Growth          | 
 
• Bone metabolites, growth factors and hormones
 
                                                                                                                                                |
|                  | Neurocognition  | 
 
• Blood markers related to brain function such as brain-derived neurotrophic factor (BDNF) and serotonin
 
                                                                                       |
|                  | Genetics        | 
 
• Epigenetics and genes related to the study outcomes, and research questions (single nucleotides polymorphisms (SNPs) and genome wide association studies (GWAS), NOT full genome sequencing)
 
 |
| Hair strands     | Stress          | 
 
• Cortisol and related metabolites
 
                                                                                                                                                             |
| Salivary samples | Stress          | 
 
• Cortisol and related metabolites
 
                                                                                                                                                             |

#### 4.9 Contact to study participants after completion of the study

After the participant has completed the 12 weeks intervention period the study staff members may contact some of the parents to the participating children to ask whether the child/parents would like to participate in small videos and interviews about the research project. Participation in these activities is completely voluntary and has no influence on the participation in the research project.

## **5. STATISTICAL CONSIDERATIONS**

### **5.1 Statistical power**

The primary outcomes of the study will be diastolic blood pressure and plasma triacylglycerol. Power calculations were performed using data from our previously conducted OPUS School Meal Study (23). With 150 completing children we will have 80% power to detect a difference of less than 0.5 SD of the outcomes i.e. 2.7 mmHg in diastolic blood pressure and of 0.13 mmol/L in triacylglycerol between the two intervention groups, respectively. This would correspond to approximately 4% reduction in blood pressure and 20% reduction in plasma triacylglycerol among this age group, which is considered relevant and obtainable.

The cognitive measurements will be secondary and exploratory outcomes, and therefore not subject to power calculation. However, in the OPUS School Meal Study we previously found that school meals rich in fish improved school performance and reading comprehension in Danish 8-11 year-olds (52). Although the sample size was about 4 times larger in that study, the fish group of FiSK Junior will get 5-10 times more n-3 LCPUFA than in the school meal study, and therefore we expect FiSK Junior to have a sufficient sample size for the cognitive outcomes as well.

### **5.2 Statistical analysis**

The effect of the intervention on the outcomes will be evaluated using analysis of covariance including baseline outcome values as covariate. Outcomes will also be analyzed with gender and genotype as potential effect modifiers.

## **6. COMPLIANCE MEASUREMENT**

The content of n-3 LCPUFA in erythrocytes will be used as biomarker of compliance, reflecting intakes over the last 3-4 months. Also, during the 12 weeks intervention period parents will be asked to register the child's intake of study foods as another measure of compliance.

## **7. RISKS, SIDE EFFECTS AND DRAW-BACKS**

There is no substantial risk associated with participation in the intervention.

### **7.1 Safety of study foods**

Apart from healthy nutrients, fish may contain unwanted substances stemming from human and natural contamination of the seas. Therefore we have thoroughly considered the safety aspects of

the study foods in collaboration with senior advisor and toxicologist [name], Division of Risk Assessment and Nutrition, National Food Institute, Technical University of Denmark (DTU FOOD). Two groups of substances are of special interest in relation to safety of fish intake: 1) Mercury and 2) Dioxins and dioxin-like polychlorinated biphenyls (PCB). Children in the intervention group will consume up to 300 g oily fish per week and the main types provided will be aqua cultured salmon (the most commonly eaten source of salmon in Denmark), some mackerel and small amounts of herring. All will be products that are available in Danish supermarkets and commonly eaten by Danes. The content of mercury and toxic equivalents (TEQ) of dioxin and dioxin-like PCB in these fish types are shown in Table 3. Mercury is mainly an issue in large predator fish such as tuna, shark and ray fish, which will not be used in the study.

**Table 3. Concentration of contaminants in study fish**

|                      | Mercury
(mg per kg fish) | Dioxin and dioxin-like PCB
(ng TEQ per kg fish) |
|----------------------|------------------------------------|-----------------------------------------------------------|
| Aqua cultured salmon | 0.021 (0 - 0.059)                  | 0.57 (0.35 - 1.4)                                         |
| Mackerel             | 0.039 (0.009 - 0.36)               | 0.87 (0.12 - 9.7)                                         |
| Herring              | 0.05 (0.010-0.23)                  | 1.2 (0.27-5.2)                                            |

Data is shown as upper bound mean (min-max). Upper bound mean implies that concentrations below the limit of detection have been substituted with the value of the limit, i.e. a likely overestimate. Values for salmon are from (53); values for mackerel and herring are from (54).

Assuming an intake of 200 g salmon + 80 g mackerel + 20 g herring every week the children will have an intake of 8.3 µg mercury and 208 pg dioxin and dioxin-like PCB per week. The European Food Safety Authority (EFSA) has established a tolerable weekly intake (TWI) for these substances, i.e. the estimated amount that can be ingested weekly over a lifetime without appreciable health risk. The TWI is 1.3 µg/kg bodyweight for methyl-mercury (55) which is the most common form of mercury in marine foods. The TWI for dioxin and dioxin-like PCB is 14 pg TEQ/kg bodyweight (56). Danish children 8 years of age have a median bodyweight of 27.5 kg (57,58). Assuming that all mercury in the fish is methyl-mercury, the TWI for the youngest children in the study will therefore be  $1.3 \mu\text{g/kg} \times 27.5 \text{ kg} = 36 \mu\text{g}$  per week for methyl-mercury and  $14 \text{ pg TEQ/kg} \times 27.5 \text{ kg} = 385 \text{ pg TEQ}$  per week for dioxin and dioxin-like PCB. Hence the study fish will provide 23% and 54% of the children's TWI for mercury and for dioxin and dioxin-like PCB, respectively.

Fish is the main source of mercury in the general Danish diet, whereas fish contributes about 30% of the intake of dioxins and PCB in the general population (59). The remaining 70% comes from milk, cheese, meat, and fats. DTU-FOOD has estimated the total mean intake of dioxin and PCB among Danish 4-14 year-olds to be 0.87 pg/day per kg bodyweight. As fish contributes 30% to this intake the children in the study are expected to have an intake of 0.61 pg/day per kg bodyweight or 4.3 pg/week per kg body weight from non-fish sources. The contribution from the study fish will be an estimated  $208 \text{ pg/week per child} / 27.5 \text{ kg} = 7.6 \text{ pg/week per kg body weight}$ . We assume that the study fish will be the only source of fish in the children's diet. The total intake of dioxin and dioxin-like PCB will therefore be  $4.3 + 7.6 = 11.9 \text{ pg/week per kg bodyweight}$  which is well below

the TWI of 14 pg/kg bodyweight. In agreement with the risk analyses conducted by DTU-FOOD in this field, we expect that the variation in the contribution to the intake of dioxin and dioxin like PCBs from the study fish will be small, i.e. for almost all children the actual intake will be close to 208 pg/week. Moreover, the families will be instructed that the study fish must replace some of the meat in the diet, which in Denmark contribute with 18% to the total intake of dioxin and dioxin like PCB. Therefore the actual intake of dioxin and dioxin-like PCB is likely to be even lower than calculated. **Altogether, it is unlikely that children in the fish group will have an intake of mercury or dioxin and dioxin-like PCB that exceed the tolerable weekly intake (TWI) during the intervention.**

Children in the control group will consume up to 300 g poultry as part of the study, mainly chicken as chicken legs and breast, but also other products such as chicken liver pâté and sausage, i.e. products that are available in most supermarkets and commonly eaten by Danes. Poultry do not contain significant amounts of harmful substances. Danish 4-9 year-olds consume on average almost 600 g (5) meat and meat products per week (2). As in the fatty fish group, families in the control group will be instructed to substitute the poultry and poultry products for some of the meat and fish normally eaten, to avoid an overly high protein intake.

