**Figure 1. Flow diagram of the study activities**

### 3.2 Study foods

Participants in the intervention group will receive oily fish (with minimum 2 g of fat per 100 g) primarily as fillets of salmon, but also other types of fatty fish such as mackerel in tomato sauce and marinated herring, whereas participants in the poultry group will receive primarily chicken and chicken products (e.g. liver pate, chicken sausage) but possibly also small amounts of duck and turkey. As far as possible, the products provided to the two groups will be matched for energy and fat content. The parents will be instructed that the study fish and poultry should substitute some of the fish and meat usually consumed by the child. Apart from this, the parents will be instructed to maintain the child's usual dietary and physical activity habits during the intervention. The participants will be asked to consume 300 g/week of fish or poultry, operationalized as two times per week as dinner meal and as bread topping / for lunch three times per week, based on typical portion sizes as estimated by the National Food Institute, Technical University of Denmark (49). The goal of 300 g per week is within the national recommendation (1) and will provide

approximately 1 g/day n-3 LCPUFA, which has been shown to reduce blood pressure and plasma triacylglycerol in previous fish oil trials (11,14,15).

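### The dioxin margin in section 7.1 is worked out for one median-weight child who eats no other fish; the diet instruction does not secure that case, and no lighter child is shown (minor, cheap to improve)

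*Protocol*

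**What the plan says.** Section 7.1 assumes 200 g salmon, 80 g mackerel and 20 g herring a week, takes mean contaminant levels from Table 3, and divides by one body weight: "Danish children 8 years of age have a median bodyweight of 27.5 kg". It adds a background from non-fish sources and sets habitual fish to zero: "We assume that the study fish will be the only source of fish". The total is 11.9 pg/kg/week against a TWI of 14, described as well below it. The only variation discussed is in the amount of dioxin from study fish per child, which is expected to be small: "for almost all children the actual intake will be close to 208 pg/week".

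The instruction to families appears in three places. Section 3.2 says that "study fish and poultry should substitute some of the fish and meat usually consumed by the child", and otherwise asks parents to keep the child's usual diet. Section 7.1 says that the "study fish must replace some of the meat in the diet, which in Denmark contribute with 18" per cent of total dioxin intake. The paragraph on the control group in section 7.1 implies that both groups are told to replace some meat and fish.

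Section 3.5.1 admits children who eat fatty fish up to once a week and sets no weight criterion. Sections 7.1 and 9.4.1 conclude that the study foods are safe for the participants.

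**The concern.** The conclusion covers all children in the fish group, but the supporting figure covers one. Two inputs decide the margin, and neither is varied.

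- **Body weight.** If the dioxin from study fish is nearly the same for every child, intake per kg rises as weight falls. By definition about half of 8-year-olds weigh less than the median, and no lower weight is worked out.
- **Other fish.** Asking families to replace some of a combined pool of fish and meat is compatible with dropping all other fish, but does not require it. A family that takes the 300 g wholly out of meat and keeps its usual fish has followed the instruction, yet falls outside the case on which the total rests.

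At stake is how far a reader, such as the ethics committee, can rely on the stated margin for a lighter child or one who goes on eating other fish.

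**Working it through.** **Inputs from the protocol**

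- Table 3 means: salmon 0.57, mackerel 0.87, herring 1.2 ng TEQ/kg (numerically equal to pg per g).
- Background, section 7.1: 0.87 pg/kg/day in total, 30% from fish and 18% from meat.
- Meat intake, section 7.1: Danish 4-9-year-olds "consume on average almost 600 g (5) meat and meat products per week".
- Usual fish, section 1.2.1: median about 70 g/week in the same age group.
- TWI 14 pg/kg/week; weight 27.5 kg.

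**Assumption added here:** dioxin is proportional to grams within each food group, and study fish displaces other food gram for gram.

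**Reproducing the protocol's figure**

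- Study fish: 200 × 0.57 + 80 × 0.87 + 20 × 1.2 = 207.6 pg/week (stated 208); 207.6 / 27.5 = 7.55 pg/kg/week (stated 7.6).
- Total background: 0.87 × 7 = 6.09 pg/kg/week. Non-fish 70% = 4.263 (stated 4.3); fish 30% = 1.827; meat 18% = 1.096.
- Total: 7.549 + 4.263 = 11.81, or 11.9 with the protocol's rounding; 11.9 / 14 = 85%.

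The protocol's sums are correct.

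**Varying the two inputs**

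Total at weight w = B + 207.6 / w, and the weight at which the total equals 14 is 207.6 / (14 − B). B is the background per kg after substitution. Each gram of meat displaced lowers B by 1.096 / 600.

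| Case | B | Total at 27.5 kg | % of TWI | Weight at which 14 is reached |
|---|---|---|---|---|
| Protocol: no other fish, no meat offset | 4.263 | 11.8 | 84 (85 as rounded) | 207.6 / 9.737 = 21.3 kg |
| 70 g fish and 230 g meat replaced | 4.263 − 0.420 = 3.843 | 11.4 | 81 | 207.6 / 10.157 = 20.4 kg |
| 35 g fish and 265 g meat replaced | 4.263 + 0.914 − 0.484 = 4.692 | 12.2 | 87 | 207.6 / 9.308 = 22.3 kg |
| Usual fish kept, 300 g meat replaced | 6.09 − 0.548 = 5.542 | 13.1 | 94 | 207.6 / 8.458 = 24.5 kg |

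Relative to 27.5 kg, 21.3 kg is 22% lower and 24.5 kg is 11% lower.

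**Lower intake of study fish.** At 80% of the target (240 g, 166.1 pg/week), 14 is reached at 16.5 kg if 70 g fish and 170 g meat are replaced, and at 19.9 kg if usual fish is kept and 240 g meat is replaced.

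**The case against.** The protocol states its assumption openly, and an instruction that does not enforce an assumption is not a contradiction. Its conclusion is only that exceeding the TWI during the intervention is unlikely. Several inputs are cautious:

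- For the Table 3 means, "concentrations below the limit of detection have been substituted with the value of the limit, i.e. a likely overestimate".
- Section 7.1 speaks of up to 300 g of fish, not always the full amount.
- The meat offset is mentioned but not credited in the 11.9.
- The TWI is a lifetime standard, while exposure lasts 12 ± 3 weeks.
- The 30% fish share is a general-population figure, and children who eat fatty fish more than once a week are excluded, so it may overstate habitual fish dioxin in this sample.
- The 24.5 kg case needs the full 300 g eaten and no usual fish displaced. With study fish at two dinners and three lunches a week, that is possible but not the likeliest pattern.

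All of this stands and limits the weight of the point. It does not supply a figure for a lighter child, nor make the instruction match the assumption.

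Three stronger readings are tempting and are not supported:

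- **That children will exceed the TWI or be harmed.** No case at 27.5 kg reaches 14, and without a weight distribution the number of children below any break-even weight is unknown.
- **That the margin is nearly gone at the median weight.** Adding all usual fish with no meat displaced gives 6.09 + 7.55 = 13.6 (97%), but it requires the 300 g to displace nothing, contrary to the instruction.
- **That the median is mislabelled where the text says "the TWI for the youngest children in the study will therefore be".** Eligibility is 8-9 years, so 8-year-olds are the youngest, and the sentence before says that the weight is a median.

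The family materials are not shown and may be stricter, so only the protocol's own wording is at issue.

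**Conclusion.** The point holds as a minor, inexpensive improvement. The 11.9 pg/kg/week is correctly calculated for a median-weight 8-year-old who eats only study fish. The protocol's substitution wording does not secure the second condition, and nothing is shown for children below the first. Depending on how much usual fish is kept, the total at 27.5 kg runs from 11.4 to 13.1 (81% to 94% of the TWI), and 14 is reached between 20.4 and 24.5 kg. Calling the intake well below the limit does not convey that range.

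This rests on the protocol's contaminant means and background shares, the full 300 g eaten, and gram-for-gram displacement. Heavier children have more margin than stated. The mercury calculation (23% of its TWI) is not questioned, and the conclusion that exceedance is unlikely is not shown to be wrong.

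**What to change.** 1. In sections 3.2 and 7.1, state that in the fish group study fish replaces other fish first (at least other fatty fish) and then meat. The instruction then matches the safety assumption.
2. In section 7.1, add the total at a low weight centile for 8-year-olds from the growth charts already cited (references 57 and 58). Showing it with and without usual fish and with the meat offset takes a few lines.
3. Replace the description of the intake as well below the TWI with the margin that results. What margin is acceptable is for the sponsor and its toxicology adviser.

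The cost is one sentence of instruction, a short table and some rewording. The downsides are a slightly stricter background-diet rule in the fish arm than in the poultry arm, and a less favourable stated margin. The study-fish dose does not change.
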